### Data and safety monitoring plan

Study data are monitored by the Paediatric Pharmacologist and the Biostatistician who are not involved with the day to day management of the recruited patients. An interim analysis for neonatal outcome is scheduled after 6 months of commencement of study in the absence of documented serious adverse effects. A decision to terminate the trial will be taken by the Paediatric Pharmacologist and the principal investigator.

### Serious adverse events

A serious adverse event for this study is defined as any life-threatening events such as thrombotic events, severe hypertension or hypotension leading to death experienced by the infant following drug administrations or any other adverse event as previously described by other researchers [45]. All adverse events, both serious and non-serious, expected or unexpected, are recorded during the clinical trial and will be transmitted by the investigators to the designated competent authorities following hospital guidelines.

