### Sample size and power calculation

There was no previous study in our environment describing the efficacy of EPO administration on the outcome of HIE. Furthermore, there is a paucity of recent published data on mortality and neurodevelopmental impairment from perinatal asphyxia in our environment. Mortality rate from asphyxia was reported to be between 31.1 and 62.8% in some hospitals in Nigeria [5, 9, 10, 44]. Since no study reported the prevalence of neurodevelopmental impairment of asphyxiated babies at 2 years of life, we expected that the prevalence of a combination of the outcome of “death and neurodevelopmental impairment” at 2 years of life among moderate/ severe HIE in a resource-poor environment such as Nigeria should be higher than the prevalence of death only (31.1–62.8%). Thus, we assumed that the prevalence of “death and neurodevelopmental impairment at 2 years of life” among moderate/ severe HIE without EPO treatment in Nigeria will be about 65%. Additionally, Zhu et al. [40] in Zhengzhou, China found that 24.6% (*n* = 18/73) of babies who had EPO either died or had neurodevelopmental impairment while 43.8% who had placebo died or had neurodevelopmental impairment, giving a relative risk of 0.62 (95% CI: 0.41–0.94). Similarly, the range of protective relative risk that was reported or assumed by previous studies was between 0.65 to 0.71 [41, 45]. Hence, we utilized the power calculator in Stata version 16 statistical software (Stata Corp, USA) to calculate the minimum sample size to be 128 babies based on the assumption that 65% of infants with moderate/ severe HIE may likely die or develop neurodevelopmental impairment without treatment; assuming a protective relative risk of 0.6, 80% power and 10% loss to follow -up.

We utilized the Sarnat and Sarnat staging [43] of moderate or severe HIE for the recruitment of eligible participants (Table 2).

**Table 2 Tab2:** Sarnat and Sarnat staging [43] of moderate or severe HIE

Category	Moderate HIE	Severe HIE
1. Level of consciousness	Lethargy or obtunded	Stupor or Coma
2. Spontaneous activity	Decreased	Absent
3. Tone	Hypotonia	flaccidity
4. Posture	Distal flexion	Decerebrate state
5. Primitive reflexes		
a. Suck	Weak or biting	Absent
b. Moro reflex	Incomplete	Absent
6. Autonomic nervous system		
a. Pupils	Constricted	Deviated, dilated, or nonreactive to light
b. Heart rate	Bradycardia	Variable heart rate
c. Respirations	Periodic breathing	Apnoea

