#### Secondary outcome measures

Survival at discharge and time to discharge. Those that survived to discharge is assessed as: neurologically normal (those who had normal tone and posture, were free from seizures, has established full feed by sucking and have normal neonatal reflexes – rooting, suck, grasp, tonic neck reflex, Moro and stepping reflexes) while neurologically abnormal are those with an abnormal tone and posture, poor suck or any abnormal neonatal reflexes at discharge)Association between the levels of NRBC and NRBC/100WBC with neonatal outcomeCranial USS evidence of ventricular enlargement, parenchymal echogenicity or cystic encephalomalacia.Safety of the medications based on the presence or absence of any adverse event such as:
Hypertension: systolic blood pressure in a neonate which is above 95th percentile for age and sex on three separate occasions;Hypotension: a systolic blood pressure in a neonate which is below the 10th percentile for age and sex on three separate occasionsApnoiec attacksThrombotic events;Polycythemia: venous hematocrit of greater than 65%.Any other adverse effect noted during the hospital stay or follow up.Those with cerebral palsy are further categorized based on features present on standardized neurologic examination, and classified as mild, moderate, or severe, with hemiplegia or diplegia, using the Gross Motor Function Classification System (GMFCS) assessment system.

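### The serious-adverse-event definition has a limb with no severity condition and leaves out new events that prolong hospital stay or disable, so the serious count and the interim condition that uses it are poorly defined

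*Protocol article*

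**What the plan says.** The section Serious adverse events gives a definition in one sentence with two limbs. The first reads: "A serious adverse event for this study is defined as any life-threatening events such as thrombotic events, severe hypertension or hypotension leading to death". The rest of the sentence ties these events to the period after dosing and adds a second limb, with a single citation, reference 45: "leading to death experienced by the infant following drug administrations or any other adverse event as previously described by other researchers".

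The next sentence promises complete capture: "All adverse events, both serious and non-serious, expected or unexpected, are recorded during the clinical trial". It adds that they are passed to the competent authorities under hospital guidelines.

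Two other sections bear on the category. Secondary outcome measures lists the safety outcomes: hypertension, hypotension, apnoea, thrombotic events, polycythaemia (haematocrit above 65%) and anything else noted in hospital or at follow-up. It does not say when one of these becomes serious. Data and safety monitoring plan says that an interim analysis of neonatal outcome is "scheduled after 6 months of commencement of study in the absence of documented serious adverse effects".

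**The concern.** Seriousness is normally judged by what an event did to the patient, and expectedness by whether the event was already known. The second limb uses the second test to answer the first question. That pulls mild known effects into the serious category. It gives no help with a new harm, and a new harm is what a trial of erythropoietin as sole agent, without hypothermia, most needs to detect.

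Two things are at stake. One is the comparison of serious events between arms: a count that mixes trivial known effects with life-threatening events, and omits new disabling ones, is hard to interpret. The other is the interim condition. It refers to serious adverse effects, so its meaning depends on where this boundary lies.

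**Working it through.** No arithmetic applies and the plan has no figure to reproduce. The check is to apply the printed definition to different kinds of event and compare the result with the rest of the article.

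**Step 1: the two limbs as conditions.** Limb 1: life-threatening, after dosing. Limb 2: described in reference 45. An event is serious if either holds.

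**Step 2: apply them.**

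| Event after dosing | Limb 1 | Limb 2 | Class as printed |
|---|---|---|---|
| Mild, transient, described in reference 45 | no | yes | serious |
| Undescribed, prolongs hospital stay, not life-threatening | no | no | not serious |
| Undescribed, lasting disability, not life-threatening | no | no | not serious |
| Haematocrit above 65%, no clinical consequence | no | depends on reference 45 | cannot be told from the article |
| Fatal apnoea | yes, on the natural reading | not needed | serious |

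Under an outcome-based rule, the first row would not be serious and the second and third would be. The printed rule therefore errs in both directions.

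**Step 3: compare with the sentence on recording.** That sentence uses two separate axes, serious or not and expected or not. Assume that expected means described in reference 45. The four combinations then come out as:

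- life-threatening and described: serious
- life-threatening and undescribed: serious
- not life-threatening and described: serious
- not life-threatening and undescribed: not serious

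Every expected event is serious, and an event can be non-serious only if it is unexpected. The split can be made, but the two axes are no longer independent.

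**Step 4: the words about death.** In limb 1 these words could qualify hypotension only, both blood-pressure events, or all three examples. On the narrower readings a survived thrombosis is a clear example. On the widest, only a fatal one is. For survived severe hypertension or hypotension, a coder must fall back on the general term life-threatening.

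**Step 5: where the class is used.** The interim condition speaks of serious adverse effects, whereas the definition speaks of events. Assuming that the same category is meant, one mild event described in reference 45 would count against the condition, and a new disabling event that did not threaten life would not.

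**The case against.** The strongest reply is that limb 2 points to one cited study and not to the whole literature. In a sentence that defines serious events, it may have been meant to import that study's serious-event criteria. If those are outcome-based, much of the gap closes. This stands as a limit on the practical effect, since reference 45 is not shown. The printed words nevertheless say any other adverse event and do not say serious, so the article does not settle the matter.

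A second reply is that nothing is lost. All events are recorded and transmitted, deaths and neurodevelopmental impairment form the primary outcome, survival is assessed at every time point in Table 3, and time to discharge is a secondary outcome. This is right, and it confines the harm to classification.

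A third is that an article condenses the full protocol. That would excuse silence, but the article states a definition, and the stated rule is what misclassifies.

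A reader might infer something stronger: that death counts only through the listed examples, and that managing physicians, who know the arm, could move deaths in or out of the serious count by the cause they assign. A reader might then size this from "Mortality rate from asphyxia was reported to be between 31.1 and 62.8% in some hospitals in Nigeria". The documents do not support that reading. The examples are introduced as illustrations, so a fatal event of another kind is naturally life-threatening. The link to treatment is one of timing, and no step of cause attribution is described. The mortality range comes from reports by other hospitals. The trial's own control-arm assumption is 65% for death or impairment combined, with no separate figure for death.

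**Conclusion.** The point holds as a defect of a stated definition. Limb 2 lacks any severity or outcome condition and mixes expectedness with seriousness. New events that prolong hospitalisation or disable without threatening life fall outside both limbs. The reach of the words about death is ambiguous.

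The consequence is misclassification in the serious-event count by arm and an unclear interim condition. It is not loss of events, and no dependence of classification on arm has been shown. The primary analysis is untouched.

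No numerical size is claimed, because nothing in the documents gives the frequency of the affected events. The conclusion rests on reading limb 2 as printed, and on taking serious adverse effects in the monitoring section to mean the category defined under Serious adverse events. Sight of reference 45 could narrow the practical gap, but the wording would still need repair. The change is worth making but is not critical to the trial.

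**What to change.** Reword the definition so that seriousness is judged by outcome, identically in both arms and regardless of suspected cause. It should cover any event after the first dose that results in death from any cause, is life-threatening, requires or prolongs hospitalisation, or causes persistent disability. Take the second limb out of this definition and use the list in reference 45 only to label an event expected or unexpected.

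State whether deaths and neurodevelopmental impairment are handled as endpoints instead of individual serious-event reports. If so, tabulate them by arm at each review. Bring Secondary outcome measures and Data and safety monitoring plan into line: say when a listed safety outcome is also serious, and use one defined term in the interim condition.

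The cost is one definition and the adverse-event form. The article says that the study is under way, so events already on file would need re-coding under the new rule. Complete recording should make that feasible if the records hold the outcome of each event. The downside is that somewhat more events will be classed as serious, with some added reporting work.

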### Statistical analysis

Statistical analysis will be performed using Stata version 16.0 (Stata Corp, USA) statistical software after importing the data from the Excel spreadsheet. Descriptive statistics will be computed for socio-demographic characteristics and expressed as frequency tables and charts. Continuous variables that are normally distributed will be expressed as mean ± standard deviation (SD) while non-normally distributed continuous variables will be expressed as median and interquartile range (IQR). Association between categories of HIE and NRBC/100WBC will be tested using Students t-test. Also, the association between the grades of HIE and the degree of neurodevelopmental impairment will be conducted using the Pearson’s Chi-square. Pearson’s Chi-square will be used to compare the Gross motor function among the categories of HIE. Time to discharge, time to death and time to achieving major neurological milestones will be evaluated using the survival analysis techniques. Kaplan Meir’s plot and Cox proportional hazard regression modelling will be conducted with severity (moderate or severe) of HIE as a primary explanatory variable. At the end-point, after 2 years of follow-up, the association between intervention arm and the end point parameters will be assessed using univariable and multivariable logistic regression modelling. Two-tailed test of hypothesis will be assumed and a *P*-value < 0.05 will be taken as statistically significant level.

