#### Primary outcome measures

The primary outcome is a composite outcome of death or neurodevelopmental impairment at 18–24 months of life. Neurodevelopmental impairment (NDI) is defined as the presence of any one of the following: hypertonia or spasticity, epilepsy, delayed milestones, cerebral palsy, Gross Motor Function Classification System (GMFCS) ≥2, MDAT *Z*-score for age ≤ 1.64 or scores less than expected for age using the MDAT chart [49].

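### Pearson's chi-square for graded impairment and gross motor function ignores the order of the grades, and loses power if three or more grades are tabulated

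*Protocol article*

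**What the plan says.** The Statistical analysis section of the protocol article names Pearson's chi-square for two associations. In the first, "the association between the grades of HIE and the degree of neurodevelopmental impairment will be conducted using the" Pearson test. In the second, "Chi-square will be used to compare the Gross motor function among the categories of HIE". HIE has two categories in this trial, as the Cox model in the same section shows: "severity (moderate or severe) of HIE as a primary explanatory variable". No trend, rank or proportional-odds test is named for either outcome.

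Under Secondary outcome measures, children with cerebral palsy are "classified as mild, moderate, or severe, with hemiplegia or diplegia, using the Gross Motor Function Classification System (GMFCS) assessment system". Under Primary outcome measures, neurodevelopmental impairment (NDI) is defined as present or absent, and one of its criteria is "Gross Motor Function Classification System (GMFCS) ≥2". On error rates the section says "Two-tailed test of hypothesis will be assumed", with P "< 0.05 will be taken as statistically significant level".

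The comparison between randomised arms is a separate sentence in the same section and uses logistic regression.

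**The concern.** Mild, moderate and severe form an ordered scale, and a cut at level 2 or above makes sense only on an ordered scale. The word degree also suggests more than presence or absence. Pearson's statistic does not change if the columns are shuffled, so it discards the information that grading supplies.

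The expected pattern runs in one direction: the Background states that morbidity and mortality rise with HIE severity. For such a pattern a test with one degree of freedom is aimed at the question, whereas Pearson's test on a 2 x K table spreads the same signal over K - 1 degrees of freedom.

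What is at stake is a consistent shift in severity between moderate and severe HIE that is reported as non-significant. The children who can be graded are few, so the large-sample P-value may also be unreliable in sparse cells.

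**Working it through.** **The plan's own figure.** The article states no power for the chi-square analyses. Its one sample-size figure, for the primary outcome, is 128. Inputs from Sample size and power calculation: 65% without treatment, relative risk 0.6 (so 0.65 x 0.6 = 39%), 80% power, 10% loss. Inputs from Statistical analysis: two-sided 5%.

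- Per arm: [1.960 x sqrt(2 x 0.52 x 0.48) + 0.842 x sqrt(0.65 x 0.35 + 0.39 x 0.61)]^2 / 0.26^2 = 56.8, rounded up to 57.
- With 10% loss: 57 / 0.9 = 63.3, rounded up to 64 per arm, 128 in total.

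The figure reproduces. It concerns the treatment comparison and does not depend on the chi-square analyses.

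**Power of Pearson's test against an ordinal test.** Suppose the whole departure from independence lies along the ordered direction. Both tests then have the same noncentrality, and only the degrees of freedom differ.

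- Noncentrality for 80% power on 1 df: (1.960 + 0.842)^2 = 7.85.
- Power on k df: the probability that a noncentral chi-square (k df, noncentrality 7.85) exceeds the central 95% point on k df. For a 2 x K table, k = K - 1.

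| Ordered levels tabulated | df | Pearson power | Loss against 80% |
|---|---|---|---|
| 2 | 1 | 80.0% | 0 points |
| 3 | 2 | 70.9% | 9.1 points |
| 4 | 3 | 64.5% | 15.5 points |
| 5 | 4 | 59.5% | 20.5 points |
| 6 | 5 | 55.5% | 24.5 points |

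The 80% reference is an assumption. If the ordinal test has 50% power, the losses for 3, 4 and 5 levels are 9.9, 15.5 and 19.2 points. At 90% power they are 6.5, 11.6 and 16.0.

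**Cross-check by simulation.** 2 x K tables were simulated with a proportional-odds shift: 4,000 runs per setting, N from 50 to 115, odds ratios from 2 to 4, and 50% to 75% of children in one HIE group. The power lost by Pearson's test against the Wilcoxon test was 2 to 11 points with 3 levels, 4 to 18 with 4, 3 to 24 with 5 and 6 to 28 with 6. Every setting with three or more levels showed a loss, but its size varied widely.

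**How many children can be graded.** Only survivors can be. The inputs are 128 babies, 10% loss, and the 31.1% to 62.8% asphyxia mortality that the article cites from Nigerian hospitals.

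- 128 x 0.9 = 115.2.
- 115.2 x (1 - 0.311) = 79, and 115.2 x (1 - 0.628) = 43.

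So about 43 to 79 children can be graded, and fewer if only those with cerebral palsy are. The article gives no cerebral palsy rate. If 30% of survivors had it (an assumption for illustration), 13 to 24 children would fill a 2 x 3 table of six cells, about 2 to 4 per cell. The simulations did not go that low.

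**The case against.** The strongest objection is that the article does not say how many levels will be tabulated. NDI is defined as present or absent, and the only numerical use of the GMFCS is a binary cut. With two HIE grades, either outcome tabulated that way gives a 2 x 2 table, where Pearson's test and the trend test are in effect the same and nothing is lost. This stands, and it makes the point conditional. It does not remove it: the section speaks of the degree of impairment and of gross motor function, and the secondary outcome list has three severity grades.

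A reader might infer that this trial gives up 9 to 20 points of power. The documents do not support that as a fact. They give no number of levels, distribution, effect size or power for these analyses, and the figure of five levels does not appear in them. With so few children, nothing shows that an ordinal test would reach 80%, and a large-sample power formula is only a guide.

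A reader might also infer that the comparison of EPO with placebo is weakened. It is not: both chi-square sentences concern HIE grade, and the arms are compared by logistic regression.

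Three further points against the concern are fair. Pearson's test remains valid for ordered categories and, apart from sparse cells, keeps its type I error. It can do better against a non-monotone pattern. The tabulated proportions show the direction of a difference, even though the test does not use it. Sparse cells are also a separate matter: using the order does not cure them, but an exact version of the test addresses them.

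The article could have left the choice of test to a fuller plan. It did not: it names the test, so the choice can be commented on.

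**Conclusion.** The point holds in conditional form and is minor. If three or more ordered grades are tabulated and worse HIE shifts children towards worse grades, Pearson's chi-square is the less powerful choice. Its power is about 71% with three grades and about 60% with five, where an ordinal test has 80%. This rests on a shift wholly along the scale, equal noncentrality for the two tests, large-sample theory and an assumed number of levels. Under the article's binary definitions the loss is zero.

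The analysis concerned is a secondary association between a baseline prognostic factor and later outcome. The primary outcome, the sample size of 128 and any conclusion about EPO are unaffected.

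**What to change.** In the Statistical analysis section, state which levels of impairment and gross motor function will be tabulated against HIE grade. Where three or more ordered grades are kept, replace Pearson's chi-square with one of the following:

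- a Wilcoxon rank-sum test or an exact linear-by-linear trend test, in exact form because so few children can be graded; or
- proportional-odds logistic regression, reporting a common odds ratio with its 95% CI.

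Keep Pearson's or Fisher's exact test for binary tables (NDI yes/no, GMFCS at the stated cut) and for nominal items such as hemiplegia against diplegia.

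The change takes a sentence or two and needs no further data or patients. Its one cost is lower sensitivity to a non-monotone pattern across grades, which the article gives no reason to expect.

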## Background

Perinatal asphyxia (PA), more appropriately known as hypoxic-ischemic encephalopathy (HIE), is a condition characterized by clinical and laboratory evidence of acute or sub-acute brain injury resulting from systemic hypoxemia and/or reduced cerebral blood flow [1]. The insult to the brain can occur in-utero, intrapartum or postnatally. Hypoxic-Ischemic Encephalopathy is the commonest etiology for neonatal encephalopathies and accounts for 23% of all term newborn deaths worldwide [2]. Severe HIE occur in 0.1–0.3% of births in resource-rich countries [2, 3]. However, the incidence of HIE is greater in low and middle-income countries (LMICs) [4] occurring in nearly 35% of neonatal admissions in India while different hospital-based studies in Nigeria documented between 2.6 and 30% [5–8]. Furthermore, Ekure et al [9] reported that HIE accounted for nearly 39% of perinatal mortalities at a tertiary hospital in Lagos, South-Western Nigeria. HIE can be mild, moderate or severe. However, the majority (about 90%) of cases of HIE that present to hospitals in Nigeria were moderate to severe [10]. The morbidity and mortality from HIE increases with increasing severity [10].

Survivors of moderate/ severe HIE have a high risk of developing severe cognitive and/or motor impairment, seizure disorders, deafness, and vision loss [11, 12] Neurologic abnormality at discharge is a strong predictor of long-term neurodevelopmental delay [13]. Many biomarkers of neurological damage resulting from asphyxia have been identified and investigated [14, 15]. Biomarkers such as nucleated red blood cells (NRBC) has been demonstrated to be markedly elevated in asphyxiated newborns and can be useful in predicting adverse neurological outcomes [13–15]. Inflammatory cytokines such as Interleukin-6 (IL-6) have been shown to accumulate early in asphyxia [16, 17]. Chiesa et al. [18] reported that IL-6 concentrations were more than 300-folds in babies with HIE as compared to normal infants. Furthermore, Creatinine kinase BB (CK-BB) has been shown to predict HIE early as its rise occurs in the first hours after brain injury [19].

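### Kaplan-Meier and Cox are named for time to discharge and time to milestones although death precludes both events; with deaths censored, Kaplan-Meier overstates the proportion discharged alive or reaching a milestone

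*Protocol article*

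**What the plan says.** The Statistical analysis section treats three endpoints alike: "Time to discharge, time to death and time to achieving major neurological milestones will be evaluated using the survival analysis techniques". It then names the tools and the main covariate: "Kaplan Meir’s plot and Cox proportional hazard regression modelling will be conducted with severity (moderate or severe) of HIE as a primary explanatory variable". The article gives no rule for an infant who dies before discharge or before a milestone, and it mentions neither a competing event nor cumulative incidence.

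Three other places bear on this:

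- Secondary outcome measures lists "Survival at discharge and time to discharge". Time to milestones is not listed there as an outcome; it appears only in the analysis section.
- Sample size and power calculation reports: "Mortality rate from asphyxia was reported to be between 31.1 and 62.8% in some hospitals in Nigeria".
- Background says: "The morbidity and mortality from HIE increases with increasing severity".

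The effect of the intervention arm on the end-point parameters after two years is assigned to logistic regression, not to the survival methods.

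**The concern.** For time to death, Kaplan-Meier is the right tool. For the other two endpoints death is a competing event, because it removes the infant permanently from the chance of live discharge or of a milestone. A single-event Kaplan-Meier analysis censors such infants by default. Its complement then describes discharge in a hypothetical ward where nobody dies, not the proportion who go home.

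At the mortality the article cites, the two quantities are far apart. The comparison the article sets out is also exposed. Severity is the main explanatory variable and is itself related to death, so the amount of censoring by death differs between the groups compared. Two severity groups could have the same Kaplan-Meier curve for discharge while very different proportions leave alive.

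**Working it through.** **The article's own figure.** The control rate is 65% ("65% of infants with moderate/ severe HIE may likely die or develop neurodevelopmental impairment without treatment"). The other inputs are "assuming a protective relative risk of 0.6, 80% power and 10% loss to follow -up" and a two-sided 5% level. The EPO rate is 0.6 × 65% = 39%, and the mean of the two rates is 0.52.

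n per arm = [1.960 × √(2 × 0.52 × 0.48) + 0.842 × √(0.65 × 0.35 + 0.39 × 0.61)]² / 0.26² = 56.8, so 57. Then 57 / 0.90 = 63.3, so 64 per arm and 128 in total. The figure reproduces. It concerns the composite of death or impairment and is not affected by this point.

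**Direction.** Let d be the discharges and n the infants at risk at each discharge time.

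- One minus Kaplan-Meier, deaths censored: sum of S_KM(t−) × d/n, where S_KM falls only at discharges.
- Cumulative incidence (Aalen-Johansen): sum of S(t−) × d/n, where S falls at discharges and at deaths.

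S_KM is never below S, so the Kaplan-Meier complement is never below the cumulative incidence. It is higher once any discharge follows a death.

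**Ceiling.** This needs no timing assumption. If every infant is followed to discharge or death, and a proportion m dies first, live discharge cannot exceed 1 − m:

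- m = 31.1%: 68.9%
- m = 62.8%: 37.2%

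The Kaplan-Meier complement tends to 100%. It reaches 100% whenever the last infant on the ward leaves by discharge.

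**Gap on a given day, illustration 1.** Assumed: constant hazards and a mean time to discharge or death of 7 days. Cumulative incidence = (1 − m)(1 − e^(−t/7)). Kaplan-Meier complement = 1 − e^(−(1 − m)t/7).

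| Mortality | Day | Kaplan-Meier complement | Cumulative incidence | Gap (points) |
|---|---|---|---|---|
| 10% (assumed) | 28 | 97.3% | 88.4% | 8.9 |
| 31.1% | 14 | 74.8% | 59.6% | 15.2 |
| 31.1% | 28 | 93.6% | 67.6% | 26.0 |
| 62.8% | 14 | 52.5% | 32.2% | 20.3 |
| 62.8% | 28 | 77.4% | 36.5% | 40.9 |

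**Illustration 2, early deaths (simulated).** Assumed: mean time to death of 4 days among those who die, and all discharges after day 5. At day 28 the figures are 98.0% against 67.7% (m = 31.1%) and 97.3% against 36.6% (m = 62.8%), gaps of 30.3 and 60.7 points.

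**Illustration 3, milestones (simulated).** Assumed: 80% of survivors reach the milestone by 24 months, and deaths fall mostly in the first months. At 24 months the figures are 80.1% against 55.3% and 79.9% against 29.9%, gaps of 24.8 and 50.0 points.

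**Severity comparison.** Assume two severity groups with the same discharge hazard, 0.10 per day, and mortality at the two ends of the cited range. At day 30 the Kaplan-Meier complement is 1 − e^(−3) = 95.0% in both. The death hazard is 0.10 × m/(1 − m), that is 0.045 and 0.169 per day. Cumulative incidence is 0.689 × (1 − e^(−0.145 × 30)) = 68.0% in one group and 0.372 × (1 − e^(−0.269 × 30)) = 37.2% in the other. The curves coincide although the proportions going home differ by about 31 points.

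**The case against.** **Censoring of deaths is not stated.** This is true. The wording would also allow dead infants to stay in the risk set to the end of follow-up, or discharge to be analysed among survivors only. Coding rules often sit in an analysis plan that is not shown. However, the article is not silent on method. It names one whose default does not suit two of its three endpoints. The point therefore depends on that default being followed.

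**The Cox model is not wrong.** This stands. With deaths censored it gives a valid cause-specific hazard ratio. If severity changed only the death hazard, equal discharge hazards would be the correct answer. The hazard ratio alone, however, does not say what proportion is discharged.

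**The proportion leaving alive is reported anyway**, as survival at discharge. This limits the harm but does not correct the curve.

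**The size is uncertain.** This also stands. The cited mortality is for asphyxia in some Nigerian hospitals, not for in-hospital deaths in this trial, and every timing is assumed. In the severity illustration the upper mortality implies a mean time to exit of 1/0.269 = 3.7 days, which sits poorly with daily scoring to day 8.

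**A stronger reading** is that the analysis distorts the comparison between arms, for instance by making EPO appear to delay discharge. The document does not support this. It makes severity the main explanatory variable for these methods and assesses arm by logistic regression. An analysis of discharge by arm is not excluded, but none is set out.

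**Conclusion.** The point holds for proportions read from Kaplan-Meier curves of time to discharge and time to milestones, if deaths are censored as the named methods do by default. Two things are secure: the direction, and the ceiling of 68.9% to 37.2% for live discharge at the cited mortality against a Kaplan-Meier complement tending to 100%. The gaps on given days (about 15 to 61 points for discharge and 25 to 50 for milestones) are illustrations that depend on assumed timing.

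Trial mortality may be lower than cited. If the relative risk of 0.6 also applied to death in the EPO arm (an assumption), overall mortality would be 0.8 × 31.1% = 24.9% to 0.8 × 62.8% = 50.2%, and the ceiling 75.1% to 49.8%. The problem would remain.

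The planned comparison by severity is exposed; a comparison by arm is exposed only if it is carried out. Time to death is unaffected because death is the event. The primary outcome counts death as an event and is analysed by logistic regression, so it is unaffected too. The point is worth correcting, but it concerns a secondary outcome and a supporting analysis.

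**What to change.** In the Statistical analysis section:

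1. Present time to live discharge and time to each milestone as cumulative incidence (Aalen-Johansen) with death as a competing event, by HIE severity, and by arm if arms are compared.
2. Report the Cox model for these endpoints as cause-specific, and say so.
3. Add a Fine-Gray model (stcrreg in Stata) where a statement about proportions is wanted.
4. State how infants who die before the event are coded.
5. Keep Kaplan-Meier for time to death.

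The cost is a change of wording, slightly more analysis and output that is less familiar to clinical readers. It needs no new data, and the primary outcome and the sample size of 128 stay as they are.
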